### Statistics

#### Primary end point

The difference between smoking cessation between Clinic A and Clinic B will be estimated from the four week and six month follow up for the primary endpoint (smoking status confirmed by carbon monoxide breathalyser and salivary cotinine tests). If there is the expected higher rate of smoking cessation for Clinic A compared with Clinic B, statistical significance will be demonstrated by the χ^2^ test.

Since there are, as yet, no case-control studies that compare quit rate following the gene-based test versus quit rate without the test, the expected difference in quit rate between Clinic A and Clinic B is difficult to estimate. Two case-control studies showing only a 5-10% increase in smoking cessation involved just a single gene of small effect [11,12]. In a randomised control trial patients were given either a full explanation of the results of spirometry testing, including an estimation of lung age or just the FEV1, without explanation (control group). The group of patients who were given the full explanation had a 7.2% higher quit rate than the control group. However, data from Auckland suggest a larger uplift of quit rate with *Respiragene.* This can be explained by the superior predictive power of a 20-gene test combined with clinical history (personal history of COPD and family history of lung cancer) to give a rather more impressive estimate of cancer risk than anything previously available.

The adequacy of sample size was tested using data from smoking cessation trials that showed:

•30-40% smoking cessation at 6-months with similar protocols [27,28].

•A 48% quit rate at 2-4 weeks in subjects with high and very high lung cancer risk scores but this difference shrinks to 27% at 6 months.

•Data from Young et al [15,18] (independently verified by McBride et al [11]) that even being given an average score for lung cancer susceptibility increases smoking cessation by approximately 10%.

Therefore, with a minimum sample sizes of 30 per group the following calculations based on these estimated quit rates apply (Table 2). Statistical power of 87.1% is generally acceptable for publication (for alpha error of 5% - i.e. 5% probability of incorrectly rejecting the null hypothesis that there is no difference in the percentage values). For further detailed statistical analysis, refer to Additional file 1.

**Table 2 T2:** Summary of values from which the power of the study are estimated

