		**Control group expected quit rate as %ge**	** *Respiragene * ****group expected quit rate as %ge**	**χ**^**2 **^**calculated from four-some table**	**P value based on χ**^**2**^	**Power calculations***
8 weeks	Sample size 30/30*	70%	94%	5.9	<0.05	79.3%
	Sample size 60/60*			11.7	<0.01	96.9%
6 months	Sample size 30/30**	35%	52%	1.7	NS	36.5%
	Sample size 60/60**			6.2	<0.05	87.1%

*Telephone (alone) quit rate (see Table 1) assumed to be 20%.

**Telephone (alone) quit rate (see Table 1) assumed to be 10-15%.

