### Limitations and assumptions

Although we have estimated, based on previous smoking cessation work using this gene-based test, that the primary endpoint will show that having the test improves quit rate by 20-25%, this was based on a cohort of hospital outpatients in Auckland, New Zealand and subjects recruited from primary care may respond differently. Although we plan to recruit a minimum of 60 subjects, this may not be enough to balance unexpected and unknown confounding factors.

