### What we might find

We aim to recruit a minimum of 60 subjects to randomise 30 into group A (test group) and 30 into Group B (control group). The normal experience in NHS smoking cessation clinics is a drop-out rate of 40-50% [30-32]. We need, therefore, to attempt to recruit about 120 subjects in order to get a statistically significant result, based on the assumptions in our power calculations. We may, however, have underestimated the 6-month quit rate using the NHS local stop smoking guidelines [22] which typically involves a multi-interventional programme which includes combinations of varenicline prescriptions, breath carbon monoxide monitoring and intensive counselling giving a quit rate of 70-80% at 6-weeks.There are however no Surrey data for 6-month quit rate which we assume, on the basis of similar smoking cessation data to be about half the 6-week figure [33] ≅ 35%.

An unknown and unpredictable factor, that could skew results significantly, is the possibility that our multi-interventional approach could help to reinforce the health risk message equally for subjects in both groups. Also, the Auckland study design involved recruitment of precontemplative-contemplative smokers from a hospital outpatient setting, compared to this study that will involve primary care subjects who have volunteered to participate in a smoking cessation programme (ie smokers in the action stage of quitting). This population, therefore, could be sufficiently different to give unexpected results. However, the results of this trial will inform as to the acceptability of this approach as well as its effectiveness.

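### Table 2's six-month row for 60 per group is miscalculated: at 35% vs 52% the expected χ² is 3.5 (p = 0.06), and power is about 47% two-sided or 59% one-sided, not 87.1%

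*Protocol article*

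**What the plan says.** The Statistics section (Primary end point) names the test: "statistical significance will be demonstrated by the χ^2^ test". It sets the error rate as "for alpha error of 5% - i.e. 5% probability of incorrectly rejecting the null hypothesis that there is no difference in the percentage values". It does not say whether power is one-sided or two-sided. The calculations are introduced with "with a minimum sample sizes of 30 per group the following calculations based on these estimated quit rates apply" and shown in Table 2.

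Table 2 gives one pair of quit rates per time point, 70% vs 94% at 8 weeks and 35% vs 52% at six months. Each pair is evaluated at 30 and at 60 per group. The six-month row for 30 per group reads "35% 52% 1.7 NS 36.5"%. The row below it, "Sample size 60/60", shows no new rates and gives χ² 6.2, p<0.05 and power 87.1%. The control rate is confirmed under What we might find: "about half the 6-week figure [33] ≅ 35"%.

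The text picks the 87.1% out as adequate: "Statistical power of 87.1% is generally acceptable for publication". What we might find then sets an aim of about 120 recruits, relying on the power calculations to reach significance.

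**The concern.** At fixed rates and equal groups, Pearson's χ² is proportional to the number per group. The 8-week rows behave this way (5.9 to 11.7). The six-month rows do not (1.7 to 6.2). One of the two six-month rows must therefore be wrong, whatever power method was used.

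Six months is the time point of the article's Hypothesis section, and the faulty row is the only one showing adequate power there. If 87.1% is wrong, a reader is told that the trial would very probably detect the assumed six-month effect when its chance is much closer to even. A non-significant six-month result could then be given more weight against the gene-based test than the design supports.

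**Working it through.** **Inputs** (Statistics section and Table 2): p₁ = 0.35, p₂ = 0.52, d = 0.17, n = 60 per group, α = 0.05. Mean rate p̄ = (0.35 + 0.52)/2 = 0.435. Sidedness is not stated, so both versions are shown.

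**Formulas**
- Expected χ² = n d² / [2 p̄(1 − p̄)]
- Power = Φ[(d − z·SE₀)/SE₁], with SE₀ = √[2p̄(1 − p̄)/n] and SE₁ = √{[p₁(1 − p₁) + p₂(1 − p₂)]/n}; z = 1.960 two-sided, 1.645 one-sided

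**Step 1. Reproduce the plan's other rows.**

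| Row | χ² stated | χ² recomputed | Power stated | One-sided 5% | Two-sided 5% |
|---|---|---|---|---|---|
| 8 weeks, 30/30 | 5.9 | 5.85 | 79.3% | 79.3% | 68.6% |
| 8 weeks, 60/60 | 11.7 | 11.71 | 96.9% | 96.9% | 93.8% |
| 6 months, 30/30 | 1.7 | 1.76 | 36.5% | 37.4% | 26.1% |
| 6 months, 60/60 | 6.2 | **3.53** | 87.1% | **59.4%** | **46.7%** |

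Three of the four rows agree with this formula at one-sided 5%, two exactly and one within a point. Only the last fails, and it fails on both χ² and power.

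**Step 2. χ² for the disputed row.** 60 × 0.17² / (2 × 0.435 × 0.565) = 1.734 / 0.49155 = 3.53, p = 0.060. The same answer follows from the table: 2 × 1.76 = 3.53, or 2 × 1.7 = 3.4 from the rounded entry. With whole counts of 21/60 vs 31/60, χ² = 3.39 and p = 0.065.

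**Step 3. Power for the disputed row.** SE₀ = √(0.49155/60) = 0.0905. SE₁ = √[(0.2275 + 0.2496)/60] = 0.0892.
- Two-sided: (0.17 − 1.960 × 0.0905)/0.0892 = −0.083, power 46.7%
- One-sided: (0.17 − 1.645 × 0.0905)/0.0892 = 0.237, power 59.4%

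**Step 4. Other methods.** Two-sided power is 47.9% with unpooled variance, 47.1% with the arcsine method, 48.0% by exact enumeration of the χ² test, and 40.6% by enumeration with continuity correction. One-sided with unpooled variance gives 60.3%. None comes near 87.1%.

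**Step 5. Rounding of the rates.** Stretching them to 34.5% vs 52.5% gives χ² 3.95, with power about 51% two-sided or 64% one-sided. That moves p just under 0.05 but still leaves χ² well below 6.2 and power well below 87.1%.

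**Step 6. What would be needed.** At 35% vs 52%, 80% power takes 133 per group two-sided (105 one-sided), and 87.1% takes 161 (130 one-sided). With 60 per group, 35% vs 60% has 79.0% two-sided power by the formula and 80.3% by enumeration.

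**The case against.** **Additional file 1 may hold more detail.** It is not shown here. It cannot, however, reconcile two rows of one table that share the same rates and differ only in sample size.

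**The authors may have intended one-sided power.** The other rows show that this is how the column was computed. This part of the objection stands: 47% should not be given as the only corrected value, and putting it in one cell would mix conventions within the column. It does not save the row, because the same basis gives about 59%.

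**The article is candid about uncertainty.** It calls the difference hard to estimate, warns that its numbers may be too few, and prints the six-month 30/30 row as non-significant with 36.5% power. That is fair, and it weakens any claim that adequacy is asserted without qualification. But these caveats concern whether the assumed rates are right. They do not correct the power calculated from those rates.

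**The 20-25% improvement under Limitations and assumptions.** The article says "that the primary endpoint will show that having the test improves quit rate by 20-25"%, and a reader might infer a conflict with the 17 points used at six months. The documents do not support that. The primary endpoint also covers 8 weeks, where Table 2's difference is 24 points, so the sentence need not be brought to 17.

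**Conclusion.** The six-month row for 60 per group is wrong as printed. For 35% vs 52%, χ² should be 3.5 rather than 6.2 and the p-value 0.06 rather than below 0.05. Power is overstated by about 40 percentage points (87.1 − 46.7) two-sided or 28 (87.1 − 59.4) one-sided. This rests on the table's own rates, equal groups of 60 analysed in full, and a 5% level. Two-sided is the natural reading of a χ² test against no difference, but the article does not say so.

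Three stronger readings go too far:
- A reader might infer that 87.1% was computed for 35% vs 60%, since one-sided power there is 87.1%. The expected χ² for that pair is 7.5, not 6.2, so the match is to one cell only and the source of the figure is unknown.
- A reader might infer that the whole trial is underpowered as assumed. The 8-week row at 60 per group stands, at 93.8% even two-sided.
- A reader might infer that the six-month comparison must be recast as estimation. An arithmetic error does not require that.

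**What to change.** 1. Correct the Table 2 row for six months, 60/60, to χ² 3.5, p = 0.06, NS.
2. Declare one sidedness and put the whole power column on it. In table order, two-sided values, which fit the named χ² test, are 68.6%, 93.8%, 26.1% and 46.7%. One-sided values are 79.3%, 96.9%, 37.4% and 59.4%.
3. Withdraw the sentence calling 87.1% acceptable, and give the corrected six-month power with its sidedness instead.
4. State that 60 per group has roughly 80% two-sided power only for about 35% vs 60%.
5. Amend the sentence under What we might find so that it no longer implies that about 120 subjects will give significance at six months under the assumed rates.

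The cost is wording and one table: one row plus the rest of the power column if two-sided is chosen, or mainly the one row if one-sided is declared. No extra patients and no change to trial conduct are needed. The stated six-month power becomes much less favourable.

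### The 8-week powers in Table 2 (79.3% and 96.9%) are one-sided 5% powers, but the planned χ² test is two-sided; power at 30 per group is about 69%, not 79%

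*Protocol article*

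**What the plan says.** In the protocol article, under Statistics, Primary end point, the analysis of quit rates is fixed in one sentence: "statistical significance will be demonstrated by the χ^2^ test". The condition placed before it is directional in tone: "If there is the expected higher rate of smoking cessation for Clinic A compared with Clinic B". The alpha error is set at 5% and explained as a "5% probability of incorrectly rejecting the null hypothesis that there is no difference in the percentage values". Neither "one-sided" nor "two-sided" appears in the article.

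The sample size is justified "with a minimum sample sizes of 30 per group", with the results in Table 2. The entries that matter here are:

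| Time point | n per group | Control | Respiragene | χ² | P | Power |
|---|---|---|---|---|---|---|
| 8 weeks | 30 | 70% | 94% | 5.9 | <0.05 | 79.3% |
| 8 weeks | 60 | 70% | 94% | 11.7 | <0.01 | 96.9% |
| 6 months | 30 | 35% | 52% | 1.7 | NS | 36.5% |

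Cessation at 8 weeks is part of the primary endpoint (Outcome measures, Primary endpoint).

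**The concern.** A χ² test on a 2×2 table rejects for a difference in either direction. At 5% its critical value is 3.84, which is 1.96 squared, so a power quoted for it should use 1.96. If the power column was computed with 1.645, it describes a more lenient test than the one planned.

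The cell most affected is 8 weeks at 30 per group. It is the only entry that brings the stated minimum size near the conventional 80%. If it is overstated, a reader deciding whether 30 per group is a defensible floor is misled about the chance of missing the assumed effect.

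**Working it through.** **Inputs.** Quit rates of 70% versus 94% (8 weeks) and 35% versus 52% (6 months), and 30 or 60 per group with equal allocation, all from Table 2. Alpha of 5%, from the Statistics section.

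**Formulae.** Let d be the difference in proportions, p̄ their mean and n the size per group.

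- SE0 = √[2·p̄(1−p̄)/n] (pooled, under the null)
- SE1 = √[(p1(1−p1) + p2(1−p2))/n] (unpooled, under the alternative)
- χ² = (d/SE0)²
- Power = Φ[(d − z·SE0)/SE1], with z = 1.645 one-sided or 1.96 two-sided

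**Step 1: confirm the inputs through χ².** For 70% versus 94%, d = 0.24 and p̄ = 0.82.

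- n = 30: SE0 = 0.0992, χ² = 5.85 (Table 2: 5.9)
- n = 60: SE0 = 0.0701, χ² = 11.71 (Table 2: 11.7)

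The rates and sizes are therefore read as the authors used them.

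**Step 2: reproduce the printed 8-week powers with z = 1.645.**

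- n = 30: SE1 = 0.0942; (0.24 − 1.645 × 0.0992)/0.0942 = 0.815; Φ = 79.26% (printed 79.3%)
- n = 60: SE1 = 0.0666; (0.24 − 1.645 × 0.0701)/0.0666 = 1.870; Φ = 96.93% (printed 96.9%)

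**Step 3: the same formula with z = 1.96.**

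- n = 30: (0.24 − 1.96 × 0.0992)/0.0942 = 0.484; Φ = 68.57%
- n = 60: (0.24 − 1.96 × 0.0701)/0.0666 = 1.539; Φ = 93.81%

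**Step 4: could another two-sided method give 79.3% at n = 30?** None of those tried does.

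| Two-sided method, n = 30 | Power |
|---|---|
| Pooled variance only | 67.7% |
| Unpooled variance only | 72.1% |
| Arcsine | 73.0% |
| Continuity-corrected | 55.2% |
| Exact power, uncorrected χ² | 72.1% |
| Exact power, Yates or Fisher | 57.5% |

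At n = 60 the exact power of the uncorrected two-sided χ² test is 95.1%.

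**Step 5: six months, 30 per group.** d = 0.17, p̄ = 0.435, SE0 = 0.1280, SE1 = 0.1261.

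- z = 1.645: (0.17 − 0.2105)/0.1261 = −0.322; Φ = 37.4%
- z = 1.96: (0.17 − 0.2509)/0.1261 = −0.641; Φ = 26.1% (exact 26.6%)

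The printed 36.5% is near the first and far from the second. The small gap is consistent with rounding of the input: a Respiragene rate of 51.7%, which rounds to 52%, gives χ² = 1.70 and one-sided power 36.5%, both as printed.

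**Step 6: sidedness of the P column.** χ² = 5.85 has a two-sided p of 0.016, which fits the printed <0.05. Halved, it is 0.008, which would ordinarily be shown as <0.01, the label used one row below. So in the same row the P value follows the two-sided convention and the power the one-sided one.

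**Step 7: consequence at the minimum size.** The chance of missing the assumed 8-week effect at 30 per group is 100 − 68.6 = 31.4%, against an implied 100 − 79.3 = 20.7%. With this formula, two-sided power first passes 80% at 40 per group (39 gives 79.97%, 40 gives 81.0%).

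**The case against.** The one-sided basis is inferred. The article never states sidedness, and it refers the reader to Additional file 1, which is not shown. Its language is directional: the Hypothesis says testing should increase cessation, and the analysis sentence speaks of an expected higher rate in Clinic A. The P labels are also coarse: χ² = 11.7 has p of about 0.0006 yet is shown as <0.01. A one-sided intention cannot be excluded from the wording alone. But expecting a direction does not declare a one-sided test, and the planned test and the null of no difference are both two-sided. If a one-sided test was meant, it is undeclared and the text still needs correcting.

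A second point is that 69% depends on the formula: the exact power of the planned test is 72.1%, so the shortfall could be put at about 7 points instead of 10.7. That is fair, and both values belong in the report.

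A third is that only two of the four power entries reproduce exactly from the printed rates. This is also true. The two 8-week cells carry the argument; the six-month figure at 30 per group supports it. The six-month entry at 60 per group (87.1%) is not explained by sidedness at all: the formula gives 59.4% one-sided and 46.7% two-sided. It is a separate error.

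Finally, the practical reach is limited. Power at 8 weeks with 60 per group stays above 90%, the article rests its claim of acceptable power on 87.1% and not on 79.3%, and it concedes that 60 subjects may be too few and that about 120 should be sought. That restricts the harm mainly to one cell, but it is the cell that supports the stated minimum.

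**Conclusion.** The point holds. The 8-week powers in Table 2 are one-sided 5% values attached to a two-sided test.

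| Row | Printed | Two-sided, same formula | Two-sided, exact χ² |
|---|---|---|---|
| 8 weeks, 30/30 | 79.3% | 68.6% | 72.1% |
| 8 weeks, 60/60 | 96.9% | 93.8% | 95.1% |
| 6 months, 30/30 | 36.5% | 26.1% | 26.6% |

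The overstatement at 8 weeks is 7 to 11 points at 30 per group and 2 to 3 points at 60 per group. This rests on the rates printed in Table 2, on an uncorrected χ² test, and on reading that test as two-sided. All figures take 30 or 60 as the number analysed. The article expects otherwise for those enrolled ("The normal experience in NHS smoking cessation clinics is a drop-out rate of 40-50" per cent), and no allowance for drop-out is made in the table or here.

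**What to change.** State in the Statistics section that the χ² test is two-sided at 5%, and name the power method. Restate the Table 2 power column on that basis: with the formula that reproduces the printed 8-week values, 69% and 94% at 8 weeks and 26% at six months with 30 per group. If exact power is preferred, the corresponding entries are 72%, 95% and 27%. The six-month entry at 60 per group needs correcting for its own reason; with the printed rates, the same two-sided formula gives 47%.

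The cost is one phrase and four table entries, with no change to design or conduct. The authors lose the appearance of nearly 80% power at the minimum size and should say plainly that 30 per group falls short of it at 8 weeks.

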**Figure 1 F1:**
[figure not shown]
**Research that established the respiragene test.** Distribution of the Respiragene score in a cross-sectional study of 484 control smokers (blue) and 446 with lung cancer (red) (Total = 930) and from the prospective study of 52 lung cancer cases (green). Reference [8].

Two case-control studies showed a 5-10% increase in cessation with a single gene test of small effect [11,12]. A small smoking cessation pilot study using spirometry results and explanations using the Fletcher-Peto diagram to explain risk demonstrated that patients find this is an acceptable method and the quit rate at 12 months was 27% [13]. In a randomised control trial patients were given either a full explanation of the results of spirometry testing, including an estimation of lung age or just their forced expiratory volume in the first second (FEV1), without explanation (control group). The group of patients who were given the full explanation had a 7.2% higher quit rate than the control group [14]. Data from a hospital outpatient cohort in Auckland suggest a larger increase in quit rate with *Respiragene* test and the Auckland formula (Table 1). Subjects, who were current smokers in the pre-contemplative and contemplative stage, were randomised into either the test group or control group and only the test group had the *Respiragene test*. Counselling and follow-up was done by telephone. Using Auckland formula to incorporate the results of the *Respiragene* test, clinical data and family history a score ranging 1-12 with associated risk level (moderate risk, high risk, very high risk) was calculated and explained to test subjects. Neither group were involved in any formal smoking cessation programme. Indeed, of the 13 subjects that had managed to stop smoking, (28% of the gene-tested group), 48% quit without any medical assistance and only 52% had nicotine replacement therapy [15,16]. When compared with previous studies using telephone counselling alone [17] (Figure 2), there is a 20-25% improvement in smoking cessation with the *Respiragene* test (Table 1). The improvement in intention to quit increases from 56% before testing to 67% in smokers with an average smokers risk of lung cancer or 89% in smokers with a high risk of lung cancer [18].

**Table 1 T1:** Respiragene study in Auckland NZ (n = 43)

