**Figure 2 F2:**
[figure not shown]
**Efficacy of the variety of smoking cessation strategies.** Percent increase of success for six months over unaided attempts for each type of quitting (chart from West & Shiffman based on Cochrane review data). Totally unaided smoking cessation has a 3-6% success rate. Therefore telephone support (Table 1) increases success rate by 6% = 9-12% quit rate.

A large hospital trial using *Respiragene* for calculating lung cancer susceptibility is currently underway in the USA [19], but there are no planned UK investigations. This study fills that gap and uses the NHS framework for smoking cessation. Other studies have taken place looking at how lung functioning testing in COPD might motivate smokers to quit, suggesting that it is feasible to conduct this sort of study [13,14,20]. This protocol describes a trial to evaluate a gene-based risk test (using genetic and clinical data) as a smoking cessation motivator, in smokers wishing to participate in an NHS primary care smoking cessation clinic (in the action stage of change), alongside the usual counselling and prescribing protocol. It will differ from previous studies using gene testing as a motivator, however, in that the NHS primary care counselling and prescribing protocol will include several other motivators (CO breath testing, saliva cotinine testing and intensive counselling) whereas the Auckland trial, using the same gene test, had none of these. Also, the method of recruitment will differ in that primary care subjects will, of necessity, be different from the Auckland hospital outpatient cohort [15,16].

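### The six-month effect is 17 points in Table 2 but 20-25 points, undated, in the Limitations, and Table 2's printed 60/60 six-month results do not follow from 17 points

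*Protocol article*

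**What the plan says.** All references are to the protocol article.

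- **Table 2, six months.** The 30/30 row reads "35% 52% 1.7 NS 36.5" (per cent): control rate, test-group rate, chi-squared, significance and power. The 60/60 row uses the same two rates and prints chi-squared 6.2, p<0.05 and power 87.1%.
- **Table 2, 8 weeks.** The 30/30 row reads "70% 94% 5.9 <0.05 79.3" (per cent).
- **Statistics, Primary end point.** The text relies on the six-month 60/60 result: "Statistical power of 87.1% is generally acceptable for publication", "for alpha error of 5" per cent. It does not say whether the power is one- or two-sided. The planned test is chi-squared.
- **Limitations and assumptions.** The authors say they have estimated "that the primary endpoint will show that having the test improves quit rate by 20-25" per cent. No time point is attached. Under Outcome measures, the primary endpoint is assessed at both 8 weeks and six months.
- **Telephone comparator.** The footnote to the six-month rows of Table 2 says "Telephone (alone) quit rate (see Table 1) assumed to be 10-15" (per cent). The six-month cell for telephone counselling in Table 1 is 9-12%, and the Figure 2 caption derives the same range: "Therefore telephone support (Table 1) increases success rate by 6% = 9-12% quit rate".
- **Auckland pilot.** Table 1 shows 8 of 27 and 6 of 16 still abstinent at six months. The Background speaks "of the 13 subjects that had managed to stop smoking, (28% of the gene-tested group", with neither a time point nor a denominator.

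**The concern.** A trial should declare one target difference for each time point at which its primary endpoint is tested. Here the sample-size table gives 17 points for six months, while the Limitations give a range that excludes 17 for an endpoint that includes six months. A six-month result of about 17 points would meet the first expectation and miss the second. A non-significant result would be hard to read without knowing which difference the trial was meant to detect.

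The power statement adds to this. The protocol defends its sample size with 87.1%, and the section on what the trial might find bases recruitment of about 120 on the power assumptions. If 87.1% does not belong to 35% vs 52%, the reader has neither a settled target nor a valid power for the one that is tabulated.

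**Working it through.** **Inputs.** Control 35% and test group 52% at six months; 70% and 94% at 8 weeks; 30 or 60 per group; alpha 5% (Table 2 and Statistics). The 20-25% in the Limitations is read as percentage points. The pilot arithmetic in step 4 supports that reading.

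**Formulas.** With n per group, difference d, mean rate m = (p1+p2)/2 and z = 1.960 (two-sided) or 1.645 (one-sided):

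- chi-squared on the expected table = n·d² / [2m(1−m)]
- power = Φ{ [d√n − z√(2m(1−m))] / √(p1(1−p1)+p2(1−p2)) }

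**1. Reproducing the table.**

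| Row | Chi-squared printed / computed | Power printed | One-sided | Two-sided |
|---|---|---|---|---|
| 8 weeks, 30/30 | 5.9 / 5.9 | 79.3% | 79.3% | 68.6% |
| 8 weeks, 60/60 | 11.7 / 11.7 | 96.9% | 96.9% | 93.8% |
| 6 months, 30/30 | 1.7 / 1.8 | 36.5% | 37.4% | 26.1% |
| 6 months, 60/60 | 6.2 / 3.5 | 87.1% | 59.4% | 46.7% |

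Three rows are reproduced, exactly or within a point, and their powers are one-sided. The fourth is not.

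**2. The fourth row in full.** m = 0.435, so 2m(1−m) = 0.4916 and chi-squared = 60 × 0.0289 / 0.4916 = 3.53, p = 0.06. With whole patients it is 3.39. For power, d√n = 0.17 × 7.746 = 1.317, and the two square roots are 0.7011 and 0.6907.

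- Two-sided: (1.317 − 1.960 × 0.7011) / 0.6907 = −0.083, giving 46.7%.
- One-sided: (1.317 − 1.645 × 0.7011) / 0.6907 = 0.237, giving 59.4%.

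Unpooled, continuity-corrected and arcsine variants give at most 60.3%. A check needs no formula: with fixed rates, chi-squared doubles when n doubles. The 8-week rows do this (5.9 to 11.7). The six-month rows go from 1.7 to 6.2.

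**3. What would give the printed figures.** From a 35% base at 60/60, one-sided power of 87.1% needs 60% in the test group (25 points), where chi-squared is 7.5. Chi-squared of 6.2 needs a test-group rate between 57% and 58%. So the two printed results do not share one effect under these formulas. This is inference from arithmetic; the protocol does not state it.

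**4. Where 20-25 could come from.** Differences tabulated at 8 weeks: 94 − 70 = 24, inside the range. At six months: 52 − 35 = 17, outside. From Table 1, the pilot at six months is (8+6)/43 = 32.6%. Less 9-12% this is 20.6-23.6 points, inside the range. Less the footnote's 10-15% it is 17.6-22.6.

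**5. Where 17 could come from.** The Statistics section lists uplifts of about 10% for average-risk subjects, and 48% (2-4 weeks) or 27% (six months) for higher-risk subjects. Weighted by the pilot's 27 and 16 subjects:

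- early: (27×10 + 16×48)/43 = 24.1
- six months: (27×10 + 16×27)/43 = 16.3

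These lie close to Table 2's 24 and 17, and the footnote's range is not used.

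**6. What the choice is worth at six months (35% control).**

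| Difference | Two-sided power 30/30 | Two-sided power 60/60 | One-sided power 60/60 | n per group, 80% two-sided |
|---|---|---|---|---|
| 17 points | 26% | 47% | 59% | 133 |
| 20 points | 34% | 60% | 72% | 96 |
| 25 points | 49% | 79% | 87% | 62 |

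**The case against.** The strongest reply is that the protocol does not set two six-month targets at all. The Limitations sentence is a caveat in the Discussion, it names no time point, and the 8-week contrast of 24 points satisfies it. Table 2 is the sample-size statement, and it says 17. This largely stands. A reader might infer that six months has been fixed at two incompatible sizes, but the text does not go that far. What remains is that the sentence covers an endpoint that includes six months, without restriction, and that the pilot's six-month figures in Table 1 also fall within 20-25. The ambiguity is real even though a direct contradiction is not shown.

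A reader might also infer that the wrong telephone rate produced the 17 points. The documents do not support that. The 35% control rate comes from halving the 6-week NHS rate (section on what the trial might find), the footnote calls its figure an assumption, and step 5 reaches about 16 points without it.

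Nor can the Background's 13 quitters (28%) be set against Table 1 as 13 versus 14 of 43. The sentence gives no date and no denominator, and 13/43 is 30.2%, not 28%. Smaller effects built on that 28%, and any wide swing in power derived from them, have no footing in the protocol.

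Finally, Additional file 1 is not shown and may explain how the rates were chosen. It cannot make 35% vs 52% at 60/60 yield chi-squared 6.2.

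**Conclusion.** The point holds as an inconsistency to be reconciled. Table 2's six-month difference is 17 points. The Limitations give 20-25 points for an endpoint that includes six months and do not say when. The footnote misreports its cited source (10-15% against 9-12%), which is minor and has no demonstrated effect on the power.

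The weightier part is that the 60/60 six-month row is wrong for the rates it carries. Chi-squared is about 3.5 with p = 0.06, and power is 47% two-sided or 59% one-sided, against the printed 6.2, p<0.05 and 87.1%. The Statistics section uses that 87.1% to justify the design. If 20-25 points is the intended six-month target, two-sided power at 60/60 is about 60-79%, still below the printed figure.

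These results assume equal groups, a 35% control rate, alpha 5%, no allowance for dropout, and 20-25% read as percentage points. The conclusion about the 60/60 row does not depend on how the 20-25 is read.

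**What to change.** 1. State one six-month target difference and use it, with its time point, in both Table 2 and the Limitations. If 20-25 points refers to 8 weeks only, say so.
2. Recompute both six-month rows for that difference and state the sidedness. If 35% vs 52% is kept, the rows become chi-squared about 1.8 and 3.5, with two-sided power about 26% (30/30) and 47% (60/60), or 37% and 59% one-sided. The 87.1%, chi-squared 6.2 and p<0.05 at 60/60 must be replaced, and so must the sentence in Statistics that relies on 87.1%. State the sidedness of the 8-week rows as well, since their powers are one-sided.
3. Change the footnote's telephone rate to agree with Table 1, or give another source for 10-15%.
4. Add the time point and denominator to the Background's 13 quitters (28%), so that it can be compared with Table 1's 14 of 43.

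The cost is a few text edits and two recalculated rows, with no extra patients. The only drawback is a less favourable stated power at six months.
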